## Abstract

**Background:**

Exercise is an important and effective approach to preventing falls in older people, but adherence to exercise participation remains a persistent problem. A unique purpose-built exercise park was designed to provide a fun but physically challenging environment to support exercise in a community setting. This project is a randomised controlled trial designed to evaluate the effectiveness of an exercise intervention using an exercise park specifically designed for older people in reducing the risk of falls.

**Methods/Design:**

This study will be a parallel randomised control trial with pre and post intervention design. One hundred and twenty people aged between 60 and 90 years old will be recruited from Melbourne suburbs and will be randomly allocated to either an exercise park intervention group (EPIG) or a control group (CG). The CG will receive social activities and an educational booklet on falls prevention. The BOOMER balance test will be used as the primary outcome measure. Secondary outcome measures will include hand grip strength, two minute walk test, lower limb strength test, spatio-temporal walking parameters, health related quality of life, feasibility, adherence, safety, and a number of other psychosocial measures. Outcome assessment will be conducted at baseline and at 18 and 26 weeks after intervention commencement. Participants will inform their falls and physical activity history for a 12-month period via monthly calendars. Mixed linear modelling incorporating intervention and control groups at the baseline and two follow up time points (18 weeks and 26 weeks after intervention commencement) will be used to assess outcomes.

**Discussion:**

This planned trial will be the first to provide evidence if the exercise park can improve functional and physiological health, psychological and well-being. In addition, this study will provide empirical evidence for effectiveness and explore the barriers to participation and the acceptability of the senior exercise park in the Australian older community.

**Trial registration:**

This trial is registered with the Australian New Zealand Clinical Trials Registry - Registry No. ACTRN12614000700639 registered on Jul 3rd 2014.

**Electronic supplementary material:**

The online version of this article (doi:10.1186/s12877-015-0057-5) contains supplementary material, which is available to authorized users.

## Background

Falls are a leading cause of death and disability among older adults [1]. About one third of people aged 65 years or older fall at least once a year [1, 2]. In 2013, Australia had 14 % of its population aged 65 years and over [3] with approximately 10 % have multiple falls [4] and 20 % of those who fall experience injuries requiring medical attention [2]. In 2011–12, there were 88,386 fall related hospitalisations in Australia for people aged over 65 years, with the most common injury being hip or other lower limb fracture [5]. Hip fractures in particular are associated with high level of mortality and morbidity, with recent studies reporting that 20 % of hip fracture patients die within 12 months of injury [6], and over half do not regain pre-fracture mobility or large muscle group abilities up to two years after the fracture [7].

Most falls are associated with one or more identifiable risk factors [8] and the risk of falling has a direct association with the number of risk factors involved [9]. Physiological factors, such as lower extremity muscle weakness, gait and balance impairments and functional impairments, have been highly associated with the risk of falls and are most often targeted by preventive programmes [9]. Therefore, targeting these modifiable risk factors through exercise programmes seems to be a suitable way to reduce the risk of falls [2, 10].

Exercise programmes have been shown to be effective in reducing the risk of falling and the rate of falls [10] as they can improve muscle strength, flexibility, balance, coordination, proprioception, reaction time and gait [11]. These positive outcomes have been observed even in the very old and frail [11]. A meta-analysis identified that 50 h cumulative exercise (irrespective of exercise frequency) is needed to reduce the risk of falls [12]. A recent telephone survey applied in NSW has shown that older people’s participation to strength or balance-challenging activities was 21.0 % (95 % CI: 9.8–22.2) with only 5.3 % participating in both forms (strength and balance-challenging activities) [13]. Thus, there is a need to improve long-term participation in physical activity, which is not a common habit for most older individuals [14].

The “exercise park for older people” was originally introduced in Europe in 2009 as a novel purpose-built exercise park designed to improve muscular strength, flexibility, coordination and balance through active fun activities. The exercise park aims to inspire older people to be playful, to exercise, and to challenge their bodies, which can lead to a more active and healthier life style. Such indoor and outdoor exercise parks are widely available in Finland, Spain and China with only few operating in Australia. Preliminary data from The Netherlands suggests the purpose-built exercise parks may be safe and acceptable to older people. However, no evidence-based research exists that demonstrates the effectiveness of the exercise park in improving physical health, psychological well-being or independence. A report from The Netherlands [15] provided preliminary evidence of the feasibility of a 10 weeks exercise program with the exercise park equipment for a small sample of older people (*n* = 13), reporting high attendance (92 %), reduction in fear of falling and increased muscle strength and balance. Although these results are promising, further research is needed with a larger sample size and a longer intervention period to determine the effectiveness of the exercise park program on physical and psychological outcomes, well-being and independence of older adults, as well as determining the feasibility and acceptability of this type of program in the Australian community.

Therefore, the aims of this study are (1) to evaluate the effectiveness of such an exercise park in reducing the risk of falls and (2) to evaluate what other benefits, including psychosocial, functional and physiological, can be achieved by using this specific exercise park for 18 weeks with a structured and progressive program in community dwelling older adults using a randomised controlled trial design and (3) what benefits are sustained eight weeks after completion of the exercise park program.

## Methods and design

All procedures involved in this trial will be conducted in compliance with National Statement on Ethical Human Resource and the Australian Code for the Responsible Conduct of Research. Ethical approval has been obtained from the Human Research Ethics Committee from Victoria University, Melbourne (Application ID. HRE13-215). The study was design according to the Consolidated Standard of Reporting Trials (CONSORT) guidelines and publications associated with the trial will be reported according the CONSORT 2010 Statement [16, 17].

### Design and setting

This study will be a parallel randomised controlled trial (RCT) with pre and post intervention design (outcome assessments at baseline and at 18 and 26 weeks after participation commencement) comparing an exercise park intervention program for older people with a control group, aiming at evaluating the effectiveness of an exercise intervention using an exercise park specifically designed for older people in reducing the risk of falls.

### Participants

One hundred and twenty older people living in the community aged between 60 and 90 years old who have had one or more falls in the previous 12 months or who are concerned about having a fall will be recruited. Participants who are generally active and independent in the community with no more than a single point stick used for regular outdoors walking (at least three times per week) will be included. The aim in these inclusion criteria is to target those with mild falls risk, but who remain relatively active, using a health promotion and prevention approach.

Older adults will be excluded from this study if they have: 1) any uncontrolled non-musculoskeletal conditions that would make testing difficult and uncomfortable, such as chronic obstructive airways disease and congestive heart failure; 2) a pre-existing neurological or orthopaedic condition that affects lower limb strength (e.g.: polio, stroke); 3) any of the following foot conditions: partial foot amputation or ulceration or foot fractures; 4) any uncontrolled musculoskeletal conditions that may affect ambulation (rheumatoid arthritis, gout, etc.). Participants with heart problems (e.g. chest pain (angina), heart murmur, heart rhythm disturbance, heart valve disease or heart failure) will be required to obtain a medical clearance from their general practitioner in order to participate in this study. Participants with any documented medical condition or physical impairment that is judged by the medical practitioner to contraindicate their inclusion will be excluded. Written informed consent will be sought from the participants

### Recruitment and randomization

Participants will be recruited from Melbourne suburbs. Local senior organizations, retirement villages, community centres, senior clubs and associations in the areas around the park location will be contacted for recruitment purposes. Participants will be also recruited via community health promotion events and advertisement in local newspapers, magazines and online social networking media. Participants will be informed about the project by posters placed in healthcare facilities and places with high circulation of senior citizens and mail-out advertisements to health care practitioners in Melbourne. Participants will be randomly allocated to one of the following groups: (1) Exercise Park Intervention Group (EPIG) or (2) Control Group (CG). Block randomization stratification by gender will be undertaken, so that blocks of 12 participants will be recruited at a time, randomized into one control group of six participants and one exercise groups of six participants (Fig. 1). To accommodate couples (e.g. partners/married couples) participation, randomisation by couple will also take place. Assessors will prepare the envelopes with six paper codes (three exercise intervention and three control group) which will be added to opaque not concealed envelopes. There will be three envelopes: one for couples, one for females and one for males. Participants will be asked to pick one paper from their respective envelope and the picked paper will assign the participant to either the exercise intervention group or control group. Recruitment will be undertaken over a period of 14 months to achieve a sample size of 60 participants in each group. Assessors and participants will not be blinded to their respective group allocation (EPIG or CG).

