**Fig. 1 Fig1:**
[figure not shown]
Consort flow diagram of recruitment and randomization

Participants from the EPIG will undergo an 18-week exercise intervention. The exercise sessions will be provided two times a week (each class approximately 1 to 1.5 h duration) and will be supervised by a qualified physiotherapist or an accredited exercise physiologist. Each session will consist of 5 to 10 min warm-up exercises, followed by 45 to 75 min on the equipment stations, and will conclude with 5 to 10 min of cool down exercises. The exercise classes will include 6 to 8 participants and will be circuit-based with the warm up and cool down exercises being performed in a group and the core session being carried out in training pairs. Participants will be performing exercises that focus on strength, balance, coordination, mobility and flexibility as detailed in Tables 1, 2, 3, 4 and 5. Exercisers will be paired in stations and an exercise session can include up to eight stations (See Table 6). The intervention program will be carried out at St Bernadette’s Community Respite House, with no cost to the participants.

**Table 1 Tab1:** Strength exercises to be performed using the senior exercise park with their respective levels of progression

Exercise	Description	Functional relevance	Progressions
Push-up bar	Participant pushes body up away from the bar and brings it down towards the bar.	Strengthens arms, back and core muscles.	Standing nearly perpendicular to the bar:
			Level 1 – Wide grip.
			Level 2 – Narrow grip.
			Level 3 – Wide grip standing on a 10cm high block*.
			Level 4 – Narrow grip, standing on a 10cm high block*
			Level 6 – Narrow grip, hand release.
			Level 7 – Narrow grip, front knee tucks.
			Level 8 – Narrow grip side knee tucks.
			Level 9 - Perform the push-ups with 1 hand. Hand on shoulder line.
Modified Pull-Ups	Participant pulls body up towards the bar.	Strengthens arms, back and core muscles.	Level 1–3 – Hands narrow (undergrip), increase distance from the bar (3 distances 3 distances determined by a line on the floor).
			Level 4–6 – Hands wide (undergrip) – increase distance from the bar (3 distances)
			Level 7–9 – Hands narrow (overgrip) – increase distance from the bar (3 distances).
			Level 10–12 – Hands wide (overgrip) – increase distance from the bar (3 distances).
			If the participant reaches RPE 4/10 again, the wooden 10-cm high block can be introduced on the exercise and all levels are repeated again.

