3	Balance Stool	Calf Raises + Finger Steps
4	Sit to Stand	Rounded Snake Pipe
5	Ramp + Net + Climb Through	Sharp Snake Pipe
6	Balance Beam	Hip extension
7	Stairs	Screws / Turners
8	Step-ups	Hip Abduction

Participants in the CG will be advised to continue with their usual daily activities and will be meeting the research team every two weeks to take part in some social activities (nine meetings of two hours duration over 18 weeks of intervention). Participants from both groups will be tested at the following timelines: baseline, at the end of the intervention period (18 weeks) and two months after that (26 weeks after intervention commencement).

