### Individual and group exercise progression

Each station will include two exercises and will be performed twice by each participant. Two participants will be allocated in each station such that each participant will perform one at a time and will swap over (See Table 6). However, a participant can be exercising only with their exercise supervisor in case there is an uneven number. Participants will have different pairs and exercise supervisors on each session to stimulate social interaction. Participants will be given a resting period of 30–60 s which will be adjusted according to program progression as detailed in Table 8. The duration of each exercise will also increase based on program progression (Table 8). Rest periods between exercises will be used to discuss about difficulties and to provide further feedback. Participants will be allowed to have as many breaks as necessary to keep them performing the exercises with good technique and proper form. As some exercises such as step-ups on platform, ramp + walking through a net, and taps onto a platform can be more challenging to some participants due to the platform height, wooden blocks (L 70 cm x W 40 cm x H 10 cm) will initially be used for these participants. The same blocks will be used to make some exercises such as push-ups, pull-ups and sit to stand a bit more challenging to participants (Fig. 2).

**Table 8 Tab8:** Set time and rest for exercise progression for the 18 weeks of intervention

Week number	Set time	Rest time
1 to 2	60 s	60 s to change over and rest
3 to 8	60 s	30 s change over and rest
9 to 14	75 s	30 s change over and rest
15 to 18	90 s	30 s change over and rest

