### Data management and statistical analysis

All analyses will be conducted on an intention-to-treat basis. If there are chance imbalances in baseline participants’ characteristics, then these variables will be used as covariates. Mixed linear modelling incorporating intervention and control groups at the baseline and two follow up time points (18 weeks and 26 weeks after intervention commencement), with the number of sessions attended and baseline physical activity level as covariates, will be carried out using SPSS. Comparisons will be made for the primary outcome (BOOMER) and secondary outcomes (functional tasks, strength measures, gait parameters, health related quality of life measures, and psychosocial measures). Although the number of falls is being recorded over a period of 12 months after the commencement of participants, this study is not powered for falls outcomes. Regarding the qualitative data being collected, the interviews from EPIG participants will be analysed using a thematic analysis approach [55], as described above.

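### Couples are randomised as one unit, but the stated model names no couple term and the sample size makes no allowance for it, so standard errors may be somewhat too small

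*Protocol article*

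**What the plan says.** **Allocation.** Under Recruitment and randomization the article states: "To accommodate couples (e.g. partners/married couples) participation, randomisation by couple will also take place". Couples have their own draw: "There will be three envelopes: one for couples, one for females and one for males". One slip therefore places two people in the same arm. Each block of 12 is "randomized into one control group of six participants and one exercise groups of six participants".

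**Delivery.** Later in the same section, the description of the intervention says: "The exercise classes will include 6 to 8 participants and will be circuit-based". Controls have "nine meetings of two hours duration over 18 weeks of intervention", but the make-up of those meetings is not given. Individual and group exercise progression adds: "Participants will have different pairs and exercise supervisors on each session to stimulate social interaction".

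**Analysis.** Data management and statistical analysis specifies: "Mixed linear modelling incorporating intervention and control groups at the baseline and two follow up time points", "with the number of sessions attended and baseline physical activity level as covariates, will be carried out using SPSS". Baseline characteristics that turn out imbalanced may be added. No couple, class or block term is named.

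**Sample size.** The section gives 48 per group for an effect size of 0.5, power 0.80 and alpha 0.05, raised to 60 per group for 20% dropout. No design effect is mentioned.

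**The concern.** Two people assigned by one draw are not two independent allocations. Partners share a household, habits and probably their attendance, so their balance scores and psychosocial responses may well be alike. An analysis that treats them as unrelated counts more independent information than the trial holds. It then understates the standard error of the group contrast and rejects a true null hypothesis more often than 5% of the time.

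Group delivery raises a related question. Exercise participants train together for 18 weeks, so peer and class effects specific to the exercise arm could also make outcomes alike within a class.

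The primary comparison (BOOMER) and the secondary comparisons share one model, so a missing term would affect them all. Couple and class membership should be recorded while the trial runs, because they may be hard to reconstruct afterwards.

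**Working it through.** **The plan's own figure.** 48/(1 − 0.20) = 60. The whole allowance goes to dropout and none to clustering. As for the 48 itself, the normal approximation at effect size 0.5 gives 50 per group one-sided and 63 two-sided, and the article does not state which applies. That is a separate matter. Here it shows only that 48 contains no hidden margin for clustering.

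**Inputs.** From the article: couples drawn as units, groups of six per arm per block, classes of 6 to 8, 48 completers and 60 recruited per group. Assumed, because the article gives none: the share *f* of participants in couples, the within-couple correlation ρ, and the class intraclass correlation (ICC).

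**Couples.** Design effect DE = 1 + *f*ρ. The standard error should be larger by √DE. True two-sided type I error = 2[1 − Φ(1.96/√DE)].

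| *f* | ρ | DE | √DE | Type I error | n per group (48 × DE) | Recruited (÷ 0.8) |
|---|---|---|---|---|---|---|
| 0.1 | 0.1 | 1.01 | 1.005 | 5.1% | 49 | 62 |
| 0.2 | 0.3 | 1.06 | 1.030 | 5.7% | 51 | 64 |
| 0.3 | 0.3 | 1.09 | 1.044 | 6.1% | 53 | 67 |
| 0.4 | 0.5 | 1.20 | 1.095 | 7.4% | 58 | 73 |

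**Classes.** DE = 1 + (*m* − 1) × ICC. Since 48 counts completers, *m* should too: 6 × 0.8 = 4.8.

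| ICC | DE | √DE | Type I error |
|---|---|---|---|
| 0.02 | 1 + 3.8 × 0.02 = 1.08 | 1.04 | 5.9% |
| 0.05 | 1 + 3.8 × 0.05 = 1.19 | 1.09 | 7.2% |
| 0.10 | 1 + 3.8 × 0.10 = 1.38 | 1.17 | 9.5% |

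**Both together, a middle case.** With *f* = 0.2, ρ = 0.3 and class ICC 0.05, DE = 1 + 0.06 + 0.19 = 1.25, and the type I error is 8.0%.

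**Direction, checked by simulation.** Ten blocks of 6 + 6 with no dropout were simulated 20,000 times and analysed by a t-test that assumes independence:

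| Source of correlation | True SE / model SE | Type I error |
|---|---|---|
| None | 1.00 | 5.0% |
| One couple per group of six, ρ = 0.3 | 1.05 | 6.2% |
| Class ICC 0.05, arm-specific | 1.12 | 7.9% |
| Both of these | 1.16 | 9.1% |
| Block effect 0.05, shared by both arms | 0.97 | 4.3% |
| Shared block 0.05 plus class 0.01 | 0.99 | 4.9% |

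Couple and arm-specific class correlation inflate the error. A shared block effect, such as season, cancels from the contrast but stays in the residual variance, so ignoring it makes the test slightly conservative.

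**The case against.** The strongest reply is that the article lists no random effects at all, not even the participant effect that a repeated-measures mixed model needs. Random-effects structure is commonly left to an analysis plan, and one may exist. This has force, above all for the class term, and it is why the point is that no term is *named*, not that the model excludes one. It has less force for couples. The article itself fixes the couple as a randomisation unit, then fixes its covariates and a finished power calculation without carrying that unit through.

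A reader might go further and infer that both arms are treated in fixed groups of six, so that standard errors will certainly be too small. The article does not support that:

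- Classes hold 6 to 8 people, so a class is not always one intact group of six.
- Under Fidelity monitoring, participants with many missed sessions make them up after the 18 weeks, possibly outside their usual class.
- Pairs and supervisors rotate, although this does not mean that class membership changes.
- The control meetings are not described as keeping the same six people together.

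Season is not a reason for understated errors either. Each block is recruited together and split between the arms, so season is largely shared by both.

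Finally, every size shown here depends on assumed correlations, and with few couples the effect is slight. That stands.

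**Conclusion.** The point holds in a limited form. Partners are allocated together, the stated model names no term for this, and the sample size allows nothing for it. If partners' outcomes are positively correlated, standard errors may be somewhat too small: by 0.5% to 9.5% of the reported value, with a true two-sided type I error of 5.1–7.4%. This assumes 10–40% of participants in couples and a correlation of 0.1–0.5. The couple part is the firmest because it follows from the allocation itself, and it is modest in size.

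The class part is conditional. It needs reasonably stable classes and a correlation specific to the arm. Under an assumed ICC of 0.02–0.10 it would bring the type I error to 5.9–9.5% on its own, but a shared block effect could offset a small class effect entirely. The documents establish neither the ICC nor class stability, so no definite inflation can be claimed. The change is still worth making, since it is cheap and matches the analysis to the units randomised.

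**What to change.** 1. Record couple, randomisation block and class identifiers for every participant.
2. In the primary and secondary mixed models, add a random intercept for couple, with each single participant as a cluster of one, alongside the within-participant repeated-measures structure. Use Satterthwaite degrees of freedom.
3. Include the randomisation block and the gender stratum as model terms.
4. As a sensitivity analysis, add a random intercept for class, at least in the exercise arm, where class membership is stable. Extend it to the control arm only if the social groups are shown to have stayed together.

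**Cost.** A few sentences of analysis text and three identifier columns. With 120/12 = 10 blocks, fixed block terms use nine degrees of freedom. Intervals become somewhat wider if the correlations are real: up to about 10% for couples over the range above, and about 17% at a class ICC of 0.10 in the sensitivity analysis. If there are very few couples, the couple variance will be poorly estimated and may come out at zero, in which case the results should differ little from the model without it.

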### Limitations

This study has a number of limitations. Firstly, it has been reported that some participants who do not receive their preferred treatment may experience “resentful demoralisation” [19], may not comply with the program structure proposed, may not report accurate responses on the follow-up appointments and may even drop out from the trial [70]. This may introduce some bias which could possibly affect the internal validity of the trial. However, because their preference is being recorded before the randomization occurs, this preference will be taken into account when analysing and interpreting the results. Secondly, due to budget limitations, this study will not be blinded where the principal researcher will be conducting the assessments, the randomization and the exercise intervention. However, despite these limitations, the results of this study will be able to provide an insight on how older adults will respond to this novel and unique senior exercise park. Furthermore, this study will report the possible health benefits and well-being improvements on older people when using this exercise park and will guide further larger research trials.

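### Allocation is drawn from unconcealed envelopes of known 3:3 content run by the unblinded assessor, and the three-envelope scheme does not guarantee the stated 6:6 split per block of 12

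*Protocol article*

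**What the plan says.** All of this is in the Protocol article.

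- **Block and split** (Recruitment and randomization): allocation is blocked, with gender as the stratum. The block itself is described in these words: "blocks of 12 participants will be recruited at a time, randomized into one control group of six participants and one exercise groups of six participants".
- **Envelopes** (same section): "Assessors will prepare the envelopes with six paper codes (three exercise intervention and three control group) which will be added to opaque not concealed envelopes". Further: "There will be three envelopes: one for couples, one for females and one for males".
- **Couples** (same section): "To accommodate couples (e.g. partners/married couples) participation, randomisation by couple will also take place".
- **The draw** (same section): "Participants will be asked to pick one paper from their respective envelope". The paper drawn fixes the group.
- **Blinding** (same section): neither assessors nor participants are blinded.
- **Who does what** (Limitations): "the principal researcher will be conducting the assessments, the randomization and the exercise intervention".
- **Preference** (Treatment preference and credibility/expectation; Limitations): each participant's preferred group is asked for and recorded before randomisation.

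The article does not say whether slips are returned after a draw, when an envelope is refilled, whether it carries over to the next batch, how many women, men or couples make up a batch, or whether all 12 are enrolled before the first slip is drawn.

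**The concern.** Concealment means that nobody involved in entering or handling a participant can know or guess the coming assignment. Here the people who prepare the envelopes know that each holds three slips per arm. Nobody is blinded, so every earlier draw is known, and the envelopes are stated not to be concealed. Whoever keeps count can work out which arm has more slips left. The person in charge of the draw may also know which group the participant would prefer.

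That leaves three things open to influence, even without intent: who is enrolled and when, the order in which people draw, and how the slips are handled. The Limitations section admits the lack of blinding and puts it down to budget, but it does not mention concealment, which does not depend on that budget. In an open trial with an assessor-administered primary outcome (BOOMER), concealment is the main protection left against selection bias. Selection on characteristics that were not measured cannot be reliably repaired in the analysis.

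A smaller, separate point is that the section describes two schemes, one block of 12 split 6:6 and three separate six-slip envelopes. They need not give the same result.

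**Working it through.** **1. How far can assignments be foreseen?**

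Inputs: six slips per envelope, three per arm, contents known, earlier draws known (all from Recruitment and randomization). Assumed: drawing without replacement. Taking all C(6,3) = 20 equally likely orders and always guessing the arm with more slips left:

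| Draw | Guess is right | Already certain |
|---|---|---|
| 1 | 0.50 | 0 |
| 2 | 0.60 | 0 |
| 3 | 0.60 | 0 |
| 4 | 0.70 | 0.10 |
| 5 | 0.70 | 0.40 |
| 6 | 1.00 | 1.00 |
| Sum | 4.1 | 1.5 |

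The closed forms agree. With b = 3 slips per arm, expected certain assignments are 2b/(b + 1) = 6/4 = 1.5, which is 25% of 6. Expected correct guesses are b + (2^(2b)/C(2b,b) − 1)/2 = 3 + (64/20 − 1)/2 = 4.1, which is 68% of 6 against 50% by chance.

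**2. What bias could follow?**

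Suppose every guess is acted on, so that participants with better prognosis are steered towards a guessed exercise slot and those with worse prognosis towards a guessed control slot. Let the two kinds differ by δ in SD units, after any adjustment. The share of better-prognosis participants is then 0.683 in the exercise arm and 0.317 in the control arm, so the bias is δ × (0.683 − 0.317) = 0.367δ.

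- δ = 0.1: 0.04 SD
- δ = 0.3: 0.11 SD
- δ = 0.5: 0.18 SD

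The documents give no value for δ, so the range is an assumption. For scale, the Sample size section plans on an effect size of 0.5. The figures are upper bounds for steering by guesses from the known contents. They do not cover interference with the slips themselves.

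**3. Does the scheme give 6:6?**

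Assumed: fresh envelopes for each batch of 12, refill when empty, and one couple slip placing two people. An envelope used for six draws contributes exactly three to each arm. For k further draws, P(x exercise slips) = C(3,x) × C(3,k − x)/C(6,k).

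- *6 single women, 6 single men:* 3 + 3 = 6. The stated split is reproduced with certainty. The same holds for 12 single participants of one sex and for 6 couples.
- *8 women, 4 men:* among the women, 3 exercise slips plus 0, 1 or 2 with probability 0.2, 0.6, 0.2; among the men, 1, 2 or 3 with probability 0.2, 0.6, 0.2. P(6:6) = 0.2×0.2 + 0.6×0.6 + 0.2×0.2 = 0.44.
- *7 women, 3 men, 1 couple:* women give 3 plus 0 or 1 (0.5 each); men give 0 to 3 with probability 0.05, 0.45, 0.45, 0.05; the couple adds 0 or 2 (0.5 each). If the couple adds 0, the rest must reach 6: 0.5×0.05 + 0.5×0.45 = 0.25. If it adds 2, the rest must reach 4: 0.5×0.45 + 0.5×0.05 = 0.25. So P(6:6) = 0.5×0.25 + 0.5×0.25 = 0.25, and the exercise group can be anywhere from 3 to 9.
- *3 couples and 6 singles of one sex:* the singles give 3 and the couples an even number, so the total is odd and 6:6 cannot occur.

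Over all compositions other than the three certain ones:

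| Couples in batch | P(6:6) |
|---|---|
| 0 | 0.41–0.50 |
| 1 | 0.20–0.25 |
| 2 | 0.28–0.36 |
| 3 | 0–0.23 |

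If slips were instead returned after each draw, prediction from contents would vanish, but for 12 single participants P(6:6) = C(12,6)/2^12 = 924/4096 = 0.23.

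**The case against.** The other side has several fair points.

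- **The participant draws the slip.** No fixed sequence exists to be read in advance, and the first draw from a full envelope is a true coin toss. A reader might infer that every assignment can be foreseen. The documents do not support that: about a quarter are certain, and the rest can be guessed only with varying success. This limits the size of the problem, but a known 3:3 content and an unconcealed envelope remain.
- **Recruiting 12 at a time may close enrolment before any draw.** If so, knowledge of the remaining slips cannot change who enters the batch. The text does not settle this, and draw order and slip handling would stay open.
- **Nothing says that the principal researcher recruits.** The Limitations section lists assessment, randomisation and intervention only. A reader might infer that one person selects participants with the next slip in mind, but that link is not stated.
- **Adjustment may remove part of any bias.** The analysis section models baseline and uses imbalanced baseline variables as covariates. That helps with what is measured and not with unmeasured prognosis.
- **The split matters less than concealment.** A reader might infer that the scheme cannot deliver 6:6. It can, and for some mixes always does. Exercise classes may hold 6 to 8, so small departures are workable. If envelopes carry over between batches, the arm totals differ by at most 3 women, 3 men and 3 couples, or 3 + 3 + 6 = 12 people. This part is a conflict of wording to reconcile and not a threat to validity.

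**Conclusion.** The concealment point stands. The article states outright that the envelopes are not concealed, that assessors fill them to a known 3:3 content, and that one unblinded person randomises, assesses and treats. Given draws without replacement, 25% of assignments are certain in advance on average and 68% can be guessed. This invites selection bias but does not show that any will occur, and its size is unknown. The upper bound of about 0.04 to 0.18 SD rests on an assumed steering difference of 0.1 to 0.5 SD and on every guess being acted on, so no single figure within it should be read as a prediction.

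The split point stands in a weaker form: three separate envelopes do not guarantee 6:6 in a batch of 12. Outside a few special mixes the chance is about 0.41–0.50 without couples and 0.20–0.25 with one couple, assuming fresh envelopes per batch, refill when empty and one slip per couple.

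**What to change.** Replace the two conflicting descriptions in Recruitment and randomization with one scheme:

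1. Complete enrolment and baseline assessment for the whole cohort of 12, and fix the list.
2. Allocate all 12 in a single computer-generated draw, chosen at random from the splits that give 6:6, keep couples together and balance sex as far as possible. Such a split exists for any number of couples: when that number is odd, one arm takes one couple more and the other takes two more singles.
3. Have the draw made by a script whose output is kept, or by an existing team member who does not assess.

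With one draw per cohort, no partly used envelope is left to predict from, and the 6:6 split holds by construction.

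If sequential allocation is kept, use a pre-generated list with varying block sizes in sequentially numbered, opaque, sealed envelopes, and state how couples are handled.

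The cost is a short protocol amendment and a simple script, with no new staff. The one small drawback is that participants learn their group only once their cohort is complete.
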